## Abstract

**Background:**

Roughly one third of disability pensions in Norway are issued for mental and behavioral disorders, and vocational rehabilitation offered to this group has traditionally been dominated by train-and-place approaches with assisted or sheltered employment. Based on a more innovative place-and-train approach, Individual Placement and Support (IPS) involves supported employment in real-life competitive work settings, and has shown great promise for patients with severe mental illness.

**Methods/design:**

The study is a multicenter Randomized Controlled Trial (RCT) of IPS in a Norwegian context, involving an effect evaluation, a process evaluation, and a cost/benefit analysis. IPS will be compared to high quality treatment as usual (TAU), with labor market participation and educational activity at 12 months post inclusion as the primary outcome. The primary outcome will be measured using register data, and the project will also include complete follow-up up to 4 years after inclusion for long-term outcome data. Secondary outcomes include mental health status, disability and quality of life, collected through survey questionnaires at baseline, and after 6 and 12 months. Participants will include patients undergoing treatment for moderate to severe mental illness who are either unemployed or on sickness or social benefits. The estimated total sample size of 400–500 will be randomly assigned to the interventions. To be eligible, participants must have an expressed desire to work, and sufficient Norwegian reading and writing skills to fill out the questionnaires.

**Discussion:**

The Effect Evaluation of Individual Placement and Support (IPS) will be one of the largest randomized controlled trials to date investigating the effectiveness of IPS on competitive employment, and the first study to evaluate the effectiveness of IPS for patients with moderate to severe mental illness within a Norwegian context.

**Trial registration:**

Clinicaltrials.gov: NCT01964092. Registered October 16th, 2013.

## Background

Roughly one third of disability pensions in Norway are issued for mental and behavioral disorders [1]. The proportion is even higher among those awarded disability pension before the age of 40, where such disorders account for 58% of all awards [1]. While approximately 65% of people with severe mental illness want to work, only 15% are employed, suggesting a large gap of unmet needs [2]. There are several economic, social, and moral arguments for facilitating work participation and preventing exclusion from working life among people suffering from mental illness, and there is strong evidence suggesting that work can have beneficial effects on physical and mental health [3,4]. Concerns that competitive employment could be harmful for patients with severe mental illness are widespread, but emerging evidence has shown that work participation improves both clinical and social functioning, finances, self-esteem, and psychiatric symptoms for these patients [5–8]. These observations can be understood through different models. While a social selection hypothesis states that good health is a condition for employment, evidence shows stronger support for a social causation hypothesis where employment leads to improved health [4]. Job loss and unemployment is strongly associated with mental illness, while re-employment has been shown to reverse the negative effects of unemployment on mental health [4,9,10]. The relationship between employment and health may be partly explained by mechanisms of health behaviors such as alcohol and substance abuse, diet, physical activity, and smoking [11–13]. A Norwegian study of alcohol disorders and re-employment suggested that although some selection to unemployment does occur, the high prevalence of harmful drinking among the unemployed is mainly a result of the unemployment rather than vice versa, and that reducing unemployment could reduce alcohol problems in Norway [14].

The Norwegian welfare system provides financial aid and security for individuals unable to work. It is however important to optimize the services provided to help people to remain in working life despite episodes of health problems or periodical troubles with functioning at work.

Vocational rehabilitation and training approaches generally fall within two traditions, *train and place* or *place and train*. In the former approach, the client undergoes targeted training in an adapted or sheltered environment to acquire necessary skills, before attempting to enter competitive employment in an arena relevant to the training. At present, this tradition dominates vocational rehabilitation in Norway, with programs such as Work with assistance (AB) and Traineeship in a sheltered business (APS).

In contrast, the place and train principle represents a novel approach where the primary goal is direct employment in real-life settings, without any preceding training. Individual Placement and Support (IPS) is a prime example of a model within this tradition, where the goal is to provide professional services to help people with disabilities participate in the competitive labor market [15]. The intervention is manualized, and integrates supported employment as a component of psychological treatment rather than a separate service. It focuses on the clients’ preferences, with the philosophy that anyone who wants to work can find a regular job in the community, and that no one should be deprived of that opportunity [16–20]. A further characteristic of the IPS model is that clients are not screened for work readiness, but rather on expressed desire to work. It does not involve intermediate work experiences, transitional employment or sheltered workshops, but actively facilitates job acquisition and provides ongoing support once the client is employed. The model has got strong empirical support in the American context, with positive results in terms of both vocational and non-vocational outcomes for people with severe mental illness [21–29], especially for young adults [30]. There is also favorable evidence for IPS from studies conducted in European countries, but these have generally not reached as strong results as the studies from the US [31–33]. The IPS transportability outside the US thus remains unanswered [33]. As of yet, no studies have evaluated the effectiveness of IPS in Norway. The Norwegian context is characterized by high job security, low unemployment, and a generous welfare system, which stands out from most other contexts where IPS has been evaluated [34]. Furthermore, previous studies have all included people with severe mental illness, with no attempts to expand the target group to involve people with moderate mental illness as well.

## Methods/design

### Aims and objectives

The main aim of the study is to evaluate the effect of IPS compared to high quality TAU offered to people with moderate to severe mental illness in six IPS centers located in different Norwegian counties. We aim to address the following questions:Is IPS more effective than high quality TAU in terms of increasing labor market participation?Is IPS more effective than TAU in terms of improving mental health status and quality of life?Are there specific Norwegian policy factors that will influence the effectiveness of IPS?What are the challenges of implementing and disseminating IPS in a Norwegian context?Is IPS cost-effective compared to TAU?

### Outcome measures

The primary outcome of the study is *increased labor market participation in ordinary paid employment* or *education.* Employment and enrollment in education will be identified using register information, and will be analyzed separately, but also combined as a general indicator of increased activity on the pathways to work. Labor market participation will be operationalized by combining a) being registered in the Norwegian Labor and Welfare Administrations (NAV) State Register of Employers and Employees, and b) not receiving unemployment or sickness benefits, c) not receiving work assessment allowance or disability pension with a higher degree of disability than at study inclusion, and d) a registered annual income. This will align with the previous IPS literature, where competitive employment is defined as “permanent jobs paying commensurate wages in integrated community settings (i.e., employing nondisabled workers) and available to anyone (not just individuals with disabilities)” [33]. Educational activity will be operationalized as started or completed education as registered in the Education Statistics by Statistics Norway (SSB). To ensure comparability of results with previous IPS-studies [35], we will collect survey information to supplement the register data regarding measures of job acquisition (e.g. time from study entry to first job start), duration (e.g. cumulative numbers of weeks worked in all jobs), intensity (e.g. percentage working at least 20 hours a week), and productivity (e.g. total hours worked/wages).

The secondary outcomes, *mental health status, disability* and *quality of life*, will also be measured through survey questionnaires, in addition to questions on background and health-related variables:*Mental Health Status* will be measured using the 14-item Hospital Anxiety and Depression Scale (HADS), consisting of 2 subscales: anxiety (7 items) and depression (7 items) [36], and the 35-item Beliefs About Voices Questionnaire-Revised (BAVQ-R), consisting of 5 subscales: malevolence (6 items), benevolence (6 items), omnipotence (6 items), resistance (9 items), and engagement (8 items) [37].*Disability* will be measured using the 12-item version of the WHO Disability Assessment Schedule 2.0 (WHODAS 2.0), consisting of 6 different functioning domains: cognition (2 items), mobility (2 items), self-care (2 items), getting along (2 items), life activities (2 items), and participation (2 items) [38].*Health-related quality of life* will be measured using the health index from the EuroQol questionnaire (EQ-5D) [39].*Alcohol abuse* will be measured using the 3-item Alcohol Use Disorders Identification Test (AUDIT-C), screening test for heavy drinking and/or active alcohol abuse or dependence [40].*Drug abuse* will be measured using the Drug Use Disorders Identification Test (DUDIT), screening for drug use, drug-related problems, and/or drug dependence [41].*Subjective Health Complaints* will be measured by the 29-item Subjective Health Complaints Inventory (SHC), consisting of 5 subscales: musculoskeletal pain (8 items), pseudoneurology (7 items), gastrointestinal problems (7 items), allergy (5 items), and flu (2 items) [42].*Social support* will be measured using a revised 11-item version of the Social Support Inventory [43,44] using 2 subscales as suggested by Øyeflaten et al. [45]: directive social support (4 items) and nondirective social support (7 items).*Fatigue* will be measured by the 11-item Chalder Fatigue Questionnaire (CFQ) consisting of 2 subscales: physical fatigue (7 items) and mental fatigue (4 items) [46].

The questionnaire package was developed in collaboration with a client representative who provided input on the length, design and formulation of the information and questionnaires.

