#### Sample size calculation

Our estimates of sample size are based on international input-data from previous IPS-studies. As a general comparison, the typical sample size in the previous IPS studies range from 41 to 312 participants [33]. The studies from countries most similar to the Norwegian context include Australia (n = 41), England (n = 188), the Netherlands (n = 151), and Sweden (n = 120) [32,33]. For the non-US studies, the mean competitive employment rate was 50% for IPS and 20% for controls [33]. The study showing the lowest effect of IPS to this date came from England, with competitive employment rates of 22% for IPS and 11% for controls [48].

If we use 50% and 20% as possible rates, we will need 39 participants in each group in order to demonstrate a statistically significant difference (with a 5% significance level and power of 80%), and in a potential scenario with rates of 22% and 11%, we will need 178 participants in each group (Figure 1).

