#### Statistical analyses

The analyses will follow the “intention to treat” principle. We will apply administrative register data from NAV and SSB in order to evaluate the primary outcome of the project; labor market participation in ordinary paid employment and educational activity. Beyond giving consent at inclusion, this part of the effect evaluation is not dependent upon participants’ willingness to respond to surveys, as register data on employment, education and use of social security benefits will be complete for all participants. Consequently, common problems related to self-report such as recall bias, justification bias, and attrition will be avoided for our primary outcomes. Randomization helps to assure that there are no systematic differences between the IPS intervention and control intervention groups at baseline, in terms of both observable and unobservable characteristics. The design allows for a comparison of proportions employed in each group over time before and after inclusion, including a test of whether differences are statistically significant. Additionally, we will perform regression analysis using logistic regression models in order to a) control for any remaining variation in observable characteristics between groups, b) investigate which factors, other than IPS intervention, have an impact on labor market participation, and c) analyze heterogeneity in the response to IPS. Groups will be compared on secondary outcome measures using survey data at baseline, and after 6 and 12 months.

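### The protocol does not consistently say which comparison (employment, education or the two combined) decides the trial, and its sample size addresses employment only

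*Protocol article*

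**What the plan says.** The article describes its primary outcome in several places, and the descriptions do not agree.

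- **Abstract, Methods/design:** IPS is compared with TAU "with labor market participation and educational activity at 12 months post inclusion as the primary outcome". Two components are joined by *and*, with a time point.
- **Aims and objectives, first question:** "Is IPS more effective than high quality TAU in terms of increasing labor market participation". Education is not mentioned.
- **Outcome measures:** the primary outcome is "increased labor market participation in ordinary paid employment* or *education". Two components are joined by *or*. The same paragraph adds that they "will be analyzed separately, but also combined as a general indicator of increased activity on the pathways to work".
- **Statistical analyses:** register data serve "the primary outcome of the project; labor market participation in ordinary paid employment and educational activity", which is singular and uses *and*. Shortly afterwards the section says that problems such as "attrition will be avoided for our primary outcomes", which is plural.
- **Sample size calculation:** only competitive employment rates are used. At 50% vs 20%, 39 per group are needed, and "in a potential scenario with rates of 22% and 11%, we will need 178 participants in each group". No rate for education or for the combined indicator is given anywhere.

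The planned 400–500 participants exceed 2 × 178 = 356. The reasons given are a more heterogeneous target group and a higher expected employment rate among controls. Neither several primary comparisons nor a composite is mentioned.

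**The concern.** Three comparisons share the primary label: employment, education, and either of the two. The wording supports at least three readings: employment decides (research question and sample size), the composite decides (the *or* definition), or there are several primary outcomes (the plural). An analysis plan cannot carry out the protocol's primary outcome until one reading is chosen.

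Two things are at stake. First, if the choice stays open until results are known, or if success on any one comparison counts, the main claim is no longer tested at 5%. Second, the sample size has been justified for only one of the three. A participant in education but not in work counts as a success on the composite, so the composite's rates, and hence its power, differ from those used in the calculation.

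**Working it through.** **1. Reproduce the stated sample sizes.** The inputs from Sample size calculation are 5% significance, 80% power, and rates of 50% vs 20% and 22% vs 11%. Sidedness is not stated; two-sided reproduces both figures. The pooled-variance formula without continuity correction is

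n = [1.960·√(2p̄(1−p̄)) + 0.842·√(p₁(1−p₁)+p₂(1−p₂))]² / (p₁−p₂)²

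- 50% vs 20%: p̄ = 0.35; n = [(1.322 + 0.539)/0.30]² = 38.5, so 39.
- 22% vs 11%: p̄ = 0.165; n = [(1.029 + 0.437)/0.11]² = 177.6, so 178.

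Both match. They are calculations for employment alone. At the planned 200 and 250 per group (1:1), power for 22% vs 11% is 84.5% and 91.4%.

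**2. False-positive rate if any one of the three suffices.** Three independent tests at 5% would give 1 − 0.95³ = 14.3%. The tests are correlated, because the third outcome is the union of the first two, so this is an upper reference. Simulated null trials (225 per arm, 200,000 per scenario, three two-sided z-tests) varied employment over 11%, 20% and 30%, and education over 5%, 10% and 20%. Within-person correlation ran from the lowest possible value to +0.2. These are assumptions; the article gives no education rate. The chance of at least one significant result was 10.5% to 12.3%.

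**3. Power for the combined indicator.** If education is independent of employment, the combined rate is 1 − (1 − p_emp)(1 − p_edu). For 10% education in both arms:

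- IPS: 1 − 0.78 × 0.90 = 29.8%
- TAU: 1 − 0.89 × 0.90 = 19.9%

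This needs 298 per group for 80% power. With 22% vs 11% employment throughout, the range is:

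| Assumed education, IPS / TAU | Combined rates | n per group for 80% | Power at 200 / 250 per group |
|---|---|---|---|
| 5% / 5% | 25.9% vs 15.4% | 235 | 73% / 82% |
| 10% / 10% | 29.8% vs 19.9% | 298 | 63% / 73% |
| 20% / 20% | 37.6% vs 28.8% | 449 | 46% / 55% |
| 15% / 10% | 33.7% vs 19.9% | 161 | 88% / 94% |
| 5% / 10% | 25.9% vs 19.9% | 769 | 30% / 36% |

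If 10% in each arm are in education and none of them is also employed, the rates are 32% vs 21% and power is 70% / 80%. At 50% vs 20% employment, power is at least 99% for equal education up to 30%.

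**4. All three as co-primary with a Bonferroni split.** At 0.05/3 the employment comparison at 22% vs 11% needs 238 per group. Power is 71.8% at 200 and 82.4% at 250. This needs no education rate.

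**The case against.** The strongest defence is that the abstract, Outcome measures and Statistical analyses each speak of one primary outcome, and that *or* describes a composite whose components are also reported. On that reading there is one primary test at 5%. A rule for multiple tests may also sit in an analysis plan that is not shown, so its absence is not a fault. Both points stand, and they make the inflation conditional: nowhere does the article say that any single significant result would be called success. They do not remove the contradiction. A composite primary does not fit a first question and a sample size that leave education out, or the plural in the analysis section.

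A reader might go further and infer that the combined indicator is underpowered. The article does not support this. It gives no education rate and no overlap with employment, and the answer runs from about 30% to over 99% depending on what is assumed. The 22% vs 11% scenario is also the lowest IPS effect the article cites.

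A reader might also infer that education favours TAU, because TAU belongs to the train-and-place tradition. That does not follow either. Background and Interventions describe the training and the two TAU schemes as work in adapted or sheltered settings and help with finding a job. Only education registered in the national education statistics counts, and nothing says that either arm would change it. The 5% / 10% row above is therefore only one end of a range.

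Finally, the planned size can absorb the ambiguity in part: even the Bonferroni requirement of 238 per group lies within 200–250. This limits the damage but does not say which test decides.

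**Conclusion.** The point holds as an inconsistency in the designation of the primary comparison. It rests on the article's own text and needs no outside figure.

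The consequences are conditional. If success on any one of the three comparisons were claimed, the false-positive rate would be about 10.5–12.3%, under the assumed null rates. For the combined indicator, the supportable statement is that power has not been assessed. It can fall below 80% in the article's own conservative scenario when education is similar in both arms, and it stays above 80% if IPS also raises education (15% vs 10%) or if employment is 50% vs 20%. For employment alone the planned size is adequate at 22% vs 11%. The power figures assume equal arms of 200 or 250 and complete register data, as the article plans.

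This should be settled before outcome data are seen, because it determines what the trial's main claim is.

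**What to change.** Name one primary comparison: ordinary paid employment at 12 months from register data, tested at two-sided 5%. This matches the first research question and the sample size as calculated. Make the combined employment-or-education indicator the first secondary comparison and education alone the next. Test them in that order, each only if the one before is significant, which keeps the error over the three at 5%. Use the same wording in the abstract, Outcome measures and Statistical analyses, and remove the plural.

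The cost is a change of wording; no new data and no change to the recruitment range are needed. The downside is that a gain seen only in education could not by itself make the trial positive.

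Naming the combined indicator as primary would also end the ambiguity. In that case the sample-size statement must be restated for that endpoint, with assumed education rates and overlap given, and the first research question reworded to include education.

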#### Participants and recruitment

Eligible participants are patients currently undergoing treatment for moderate to severe mental illness, who are currently out of the labor market but have an expressed desire to work. They could be either unemployed, on sick leave benefits, or on other social benefits at the time of inclusion. Participants will primarily be recruited from the various District Psychiatric Centers (DPS), which are placed in secondary care, but could also be recruited from stepped-care initiatives located in primary care. All participants are or will be connected to a treatment-team linked to a job specialist (caseworker trained in IPS). We aim to recruit 200–250 participants in each group, with a total sample size of 400–500.

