#### Subgroups

Any significant main effects between the IPS intervention and control intervention group may allow for subgroup analyses. Regression analyses stratified on intervention group will additionally be conducted in order to study variables or sub-groups showing a stronger or weaker effect. The following a priori defined subgroups will be investigated: diagnostic groups (moderate vs. severe mental illness), work status at baseline (unemployed vs. disability benefits), and previous work history (previously employed vs. never been employed).

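### Benefits carried over from inclusion are scored differently for the unemployed and disability-benefit subgroups, so a difference between them can be partly definitional

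*Protocol article*

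**What the plan says.** Outcome measures in the protocol article builds labour market participation from four register conditions that must hold together. Condition (a) is an entry in the state register of employers and employees. Condition (b) makes no reference to baseline: "not receiving unemployment or sickness benefits". Condition (c) covers the longer-term benefits and brings in a comparison with baseline: "not receiving work assessment allowance or disability pension with a higher degree of disability than at study inclusion". The fourth condition concerns earnings: "d) a registered annual income". No minimum income or hours is attached to the last.

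Participants and recruitment admits people of mixed benefit status: "They could be either unemployed, on sick leave benefits, or on other social benefits at the time of inclusion".

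Subgroups lists, among three comparisons defined in advance, "work status at baseline (unemployed vs. disability benefits". It says that a significant main effect may open the way to subgroup analyses. It also commits to regressions run separately within each trial arm, to look for variables or subgroups with a stronger or weaker effect.

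Statistical analyses compares proportions employed and adds logistic regression for three purposes: adjustment, identifying factors other than IPS that affect participation, and "c) analyze heterogeneity in the response to IPS".

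No section links the benefit conditions to the work-status subgroup or names a benefit-independent definition for it.

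**The concern.** Condition (b) is absolute: any unemployment or sickness benefit means failure, whatever the person received at inclusion. For pension, condition (c) is relative: a pension already held may be kept in full. So a benefit carried over from inclusion is disqualifying for one subgroup and harmless for the other, and the planned comparison sets those two subgroups against each other.

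Take two people with the same part-time job at 12 months. One was on disability pension at inclusion and keeps it at the same degree: success. The other was unemployed at inclusion and still draws some unemployment benefit: failure. Because condition (d) sets no minimum, small jobs count, and these are the jobs most easily combined with a benefit.

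At stake is the answer to a question the article itself raises under Sample size calculation: which groups gain most from IPS. A difference produced by the scoring rule could be reported as effect modification, or as a prognostic effect of baseline work status.

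**Working it through.** **1. The plan's own figures.** The per-group size is n = [1.960·√(2p̄(1−p̄)) + 0.842·√(p₁(1−p₁)+p₂(1−p₂))]² / (p₁−p₂)², with two-sided 5%, 80% power and 1:1 allocation.
- 50% vs 20%: (1.322 + 0.539)² / 0.09 = 38.5, so 39.
- 22% vs 11%: (1.029 + 0.437)² / 0.0121 = 177.6, so 178.

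Both match the article (for the second, "in a potential scenario with rates of 22% and 11%, we will need 178 participants in each group"). The point does not touch these figures; they serve only as plausible job rates below.

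**2. The rule set out by baseline status**, for someone with a registered job and income at 12 months:

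| Also receiving at 12 months | Unemployed at inclusion | Disability pension at inclusion |
|---|---|---|
| Nothing | success | success |
| Unemployment or sickness benefit | failure | failure |
| Pension, degree no higher than at inclusion | cannot arise (a new pension is higher than none) | success |
| Pension, higher degree | failure | failure (cannot arise if already full) |

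The carried-over benefit is therefore a failure in the first column and a success in the second.

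**3. Illustration.** Assumptions:
- True job rates p(IPS) and p(TAU) are the same in both subgroups.
- A share f of job holders still draws the baseline benefit. The document gives no f, so a range is used.
- Pension degrees do not rise.

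In the pension subgroup the observed rates equal the true ones. In the unemployed subgroup the observed rate is p·(1−f), arm by arm.

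Example with 50%/20% and f = 0.4 in both arms: the unemployed subgroup shows 0.50·0.6 = 30% and 0.20·0.6 = 12%. The risk difference is 18 points. The odds ratio is (0.30/0.70)/(0.12/0.88) = 3.14. The risk ratio is 30/12 = 2.5, because (1−f) cancels.

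The last two columns give the chance that a Wald interaction test rejects at 5%, for a total N of 400 to 500. They assume everyone falls into one of two equal subgroups with 1:1 allocation (100 to 125 per cell).

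| True rates | f IPS / TAU | Risk difference, pension vs unemployed (points) | Odds ratio | Risk ratio | Rejects, risk difference | Rejects, log odds |
|---|---|---|---|---|---|---|
| 50/20 | 0 / 0 | 30 vs 30 | 4.00 vs 4.00 | 2.5 vs 2.5 | 5% | 5% |
| 50/20 | 0.2 / 0.2 | 30 vs 24 | 4.00 vs 3.50 | 2.5 vs 2.5 | 10.4–11.8% | 5.9–6.2% |
| 50/20 | 0.4 / 0.4 | 30 vs 18 | 4.00 vs 3.14 | 2.5 vs 2.5 | 29.1–35.0% | 7.8–8.5% |
| 50/20 | 0.4 / 0.2 | 30 vs 14 | 4.00 vs 2.25 | 2.5 vs 1.875 | 45.3–54.0% | 22.9–27.4% |
| 50/20 | 0.6 / 0.2 | 30 vs 4 | 4.00 vs 1.31 | 2.5 vs 1.25 | 87.2–93.4% | 62.5–72.1% |
| 50/20 | 0.2 / 0.4 | 30 vs 28 | 4.00 vs 4.89 | 2.5 vs 3.33 | 5.6–5.8% | 7.0–7.4% |
| 22/11 | 0.4 / 0.4 | 11 vs 6.6 | 2.28 vs 2.15 | 2.0 vs 2.0 | 10.1–11.4% | 5.1% |
| 22/11 | 0.6 / 0.2 | 11 vs 0 | 2.28 vs 1.00 | 2.0 vs 1.0 | 38.9–46.6% | 25.2–30.2% |

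Participants in neither subgroup, or the early 2:1 allocation, would make some cells smaller and these chances lower.

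**4. Within-arm regressions.** Equal f across arms gives no protection here, because the comparison is between subgroups inside one arm. With f = 0.4 and a true rate of 50% in the IPS arm, pension holders show 50% and the unemployed 30%: odds ratio (0.5/0.5)/(0.3/0.7) = 2.33. In the TAU arm, 20% against 12% gives (0.2/0.8)/(0.12/0.88) = 1.83. Both come from the definition alone. The logistic model for factors other than IPS has the same problem.

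**The case against.** The case for leaving the plan alone has real weight.

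- **One rule covers both arms.** The randomised contrast is not biased by it, overall or within a subgroup. This stands. A reader might infer that the primary result is distorted; the document does not support that.
- **The planned model is logistic.** With equal shares in both arms, the odds ratio moves little and the risk ratio not at all. This stands. A claim that half the effect could vanish rests on the risk-difference scale with a large assumed share, or on shares that differ by arm. It does not, however, rescue the comparison of proportions or the within-arm regressions.
- **Direction is open.** A reader might infer that IPS will look better for people on disability benefits. If the share is higher under TAU, the odds ratio tilts the other way (4.00 vs 4.89), so the text predicts no direction.
- **The share is unknown and may be small.** Being unemployed is a work status. The article does not say that this subgroup draws unemployment benefit, and it expects some participants never to have worked. If few combine work with benefit, the artefact nearly disappears.
- **The wording of (c) is ambiguous.** If the qualifier attaches only to pension, work assessment allowance is an absolute bar, and allowance recipients counted under disability benefits face the same kind of rule as the unemployed. The asymmetry is secure only for pension holders.
- **A relative pension rule suits an outcome framed as increased participation, and details may sit in the analysis plan.** Both are fair. But the definition and the subgroup are each fixed in the article, and their conflict follows from what is written. The supplementary job measures do not depend on benefits, but they come from surveys with an expected response of at most 60%.

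**Conclusion.** The concern holds as a limit on interpretation. The employment definition applies an absolute standard to unemployment and sickness benefit and a baseline-relative one to disability pension, and a prespecified comparison runs across that divide. Differences between the work-status subgroups, whether in IPS effect or in regressions on baseline status, can be partly definitional.

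The size cannot be fixed from the document. Over the assumed shares, with 50% vs 20% in truth, the unemployed subgroup's risk difference ranges from 28 down to 4 points against 30, and its odds ratio from 4.89 to 1.31 against 4.00. The large distortions need shares that differ by arm. With equal shares of 0.4, a false interaction on the log-odds scale appears in 7.8–8.5% of trials against a nominal 5%. The distortion is nil if no job holder keeps a benefit, and nil on the risk-ratio scale if the share is equal in both arms.

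This is a worthwhile improvement to the subgroup work. It gives no ground for doubting the main comparison, the sample size or the endpoint itself.

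**What to change.** Keep conditions (a) to (d) as the endpoint. For the work-status subgroup comparison, and for any regression on baseline work status, also report an employment definition applied identically whatever the benefit at inclusion. One example is register employment plus registered income, with the same sickness-benefit exclusion for everyone, and unemployment benefit and pension ignored. Dropping the sickness-benefit condition as well would be a mistake: someone on the employer register with some annual income but on full sickness benefit at 12 months would then count as working.

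In addition:
- report benefit receipt among the employed, by subgroup and arm, which shows the share f directly;
- state whether the higher-degree qualifier covers work assessment allowance, and whether allowance recipients belong to the disability-benefit subgroup;
- state that effect modification by baseline work status will not be claimed unless it also appears under the uniform definition.

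The cost is a few sentences and one extra analysis of register data already to be obtained. The downside is a subgroup endpoint that differs from the main one, so both results must be shown side by side. If the analysis plan already contains such a definition, a cross-reference is enough.
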